## Abstract

**Background:**

Mid-portion Achilles tendinopathy is a common condition, characterised by localised Achilles tendon load-related pain and dysfunction. Numerous non-surgical treatments have been proposed for the treatment of this condition, but many of these treatments have a poor or non-existent evidence base. Heel lifts have also been advocated as a treatment for Achilles tendinopathy, but the efficacy and mechanism of action of this intervention is unclear. This proposal describes a randomised controlled trial comparing the effectiveness of heel lifts versus sham heel lifts for reducing pain associated with mid-portion Achilles tendinopathy, with an embedded biomechanical analysis.

**Methods:**

One hundred and eight men and women aged 18 to 65 years with mid-portion Achilles tendinopathy (who satisfy the inclusion and exclusion criteria) will be recruited. Participants will be randomised, using the website Sealed Envelope, to either a control group (sham heel lifts) or an experimental group (heel lifts). Both groups will be provided with education regarding acceptable pain levels to ensure all participants receive some form of treatment. The participants will be instructed to use their allocated intervention for at least 8 h every day for 12 weeks. The primary outcome measure will be pain intensity (numerical rating scale) at its worst over the previous week. The secondary outcome measures will be additional measures of Achilles tendon pain and disability, participant-perceived global ratings of change, function, level of physical activity and health-related quality of life. Data will be collected at baseline and the primary endpoint (week 12). Data will be analysed using the intention-to-treat principle. In addition, the acute kinetic and kinematic effects of the interventions will be examined at baseline in a subpopulation of the participants (*n* = 40) while walking and running using three-dimensional motion analysis.

**Discussion:**

The LIFT trial (efficacy of heeL lIfts For mid-portion Achilles Tendinopathy) will be the first randomised trial to compare the efficacy of heel lifts to a sham intervention in reducing pain and disability in people with Achilles tendinopathy. The biomechanical analysis will provide useful insights into the mechanism of action of heel lifts.

**Trial registration:**

Australian New Zealand Clinical Trials Registry, ACTRN12623000627651. Registered 7 June 2023.

**Supplementary Information:**

The online version contains supplementary material available at 10.1186/s13063-024-08185-8.

## Introduction

### Background and rationale

Mid-portion Achilles tendinopathy (AT) is a common condition, with incidence rates reported to be 2.35 per 1000 people in the general population [1]. Athletes, particularly elite long-distance runners, are commonly affected having a lifetime risk of 52% [2]. However, the condition also affects sedentary populations, with one third of people with chronic AT being physically inactive [3]. Achilles tendinopathy typically causes localised load-related pain and stiffness, which can be debilitating and severely impact quality of life [4]. In addition, recovery times can be long (between 21 and 479 days [5]) and treatment expensive; in the Netherlands, the mean estimated costs were US $490 per patient (mostly from healthcare visits) per annum [4].

Achilles tendon loading exercise accompanied with education about limiting pain with activity is recommended as the first-line treatment for AT in clinical guidelines [6, 7] and expert narratives [8, 9]. However, the efficacy of exercise is unclear, as there are major criticisms of current research in this area, including underreporting and underpowered studies [10]. Also, exercise alone may not always be effective as up to 60% of people with AT have continued pain and disability after 5 years despite exercise interventions, and 48% will seek additional treatment including shoe inserts and surgery [11].

Heel lifts are an alternative treatment that are commonly used and recommended for mid-portion AT [12, 13]. A recent trial has supported the use of this intervention for mid-portion AT, reporting that heel lifts were more effective than eccentric calf exercise over 12 weeks for improving pain, function, and health-related quality of life [14]. However, there were limitations to this trial, including (i) participants were not blinded to the allocated intervention and (ii) there was an absence of a no treatment group (e.g. sham). Therefore, it is unclear if the efficacy of the heel lifts was due to specific treatment effects, placebo effects or other factors, such as natural history.

The classical theoretical mechanism for the use of heel lifts is that they reduce the load demands placed on the Achilles tendon (i.e. strain and peak force) by increasing the lever arm of the tendon at the ankle [15]. However, the biomechanical studies on the Achilles tendon and heel lifts thus far have been limited to small trials (i.e. 3 to 19 participants), who were all healthy [16] and may have differing responses compared to a symptomatic AT cohort. Therefore, there is currently a lack of evidence to explain the mechanism by which heel lifts exert their effects when used to treat mid-portion Achilles tendinopathy.

### Objectives

The primary aim is to examine the efficacy of heel lifts versus sham heel lifts on pain intensity among individuals with mid-portion Achilles tendinopathy at 12 weeks. The secondary aim is to investigate the acute biomechanical effects of heel lifts among individuals with mid-portion Achilles tendinopathy.

## Methods

### Trial design

The LIFT trial (efficacy of heeL lIfts For mid-portion Achilles Tendinopathy) will be a parallel group, participant- and assessor-blinded, explanatory, superiority randomised controlled trial with a 12-week follow-up (Fig. 1). Participants will be randomised to a control group (sham heel lift) or an experimental group (heel lifts). To ensure all participants (who will all have some level of pain and disability) receive some form of intervention, both groups will be provided with the same education regarding activity modification. This trial design covers any ethical concerns of not treating participants in pain and will allow the efficacy of heel lifts to be evaluated.

**Fig. 1 Fig1:**
[figure not shown]
Study protocol

This trial protocol has been reported in accordance with the Standard Protocol Items: Recommendations for Interventional Trials (SPIRIT) guidelines [17], as well as tendinopathy consensus group reporting recommendations [18]. The SPIRIT checklist is included as Additional file 1. Any changes to the trial protocol will be reported in the final publication and communicated to relevant parties, such as the Ethics Committee, trial registry and participants.

### Study setting

The initial assessment will be conducted at a single centre in the Institute for Health and Sport (Victoria University, Melbourne Australia). Publications associated with the trial will be reported according to the Consolidated Standards of Reporting Trials (CONSORT) 2010 [19, 20], and the interventions will be described using the TIDieR checklist [21]. The trial has been registered with the Australian New Zealand Clinical Trials Registry (ACTRN12623000627651).

### Ethics approval

Ethics approval has been granted from the Monash University Human Ethics Committee (no: 36420). Informed consent will be obtained from all participants (Additional File 2). Ethical standards will adhere to the National Health and Medical Research Council (NHMRC) National Statement [22] and the World Medical Association’s Declaration of Helsinki [23].

### Eligibility criteria

Participants will be recruited by mail-out and emailed advertisements to healthcare practitioners’ in Melbourne. In addition, we will advertise this trial using social media (such as Twitter, Facebook and Instagram), including paid advertisements.

All participants who meet the eligibility criteria will be included. Respondents will initially be screened by telephone interview by a single researcher (JB) to check that they are suitable for the study. Suitable participants will then attend an initial assessment for further eligibility screening. The assessing investigator (JB) is a registered podiatrist with 3 years of experience and will be supported by investigators with expertise in Achilles tendinopathy management and clinical trials (PM: registered physiotherapist; SEM: registered podiatrist).

Inclusion criteria:Aged 18 to 65 years;Symptoms of mid-portion Achilles tendinopathy in one or both lower limb(s) for > 6 weeks;Report maximum Achilles tendon pain severity experienced over the past week that is > 3 out of 10 (using a numerical pain rating scale);Regularly use footwear that can accommodate heel lifts. This is defined as using footwear that can accommodate heel lifts for at least 8 h per day [24];Be literate in English and able to complete the questionnaires used in this trial (e.g. VISA-A questionnaire);Be willing to not receive any treatment on the involved Achilles tendon(s) (other than those allocated in the current study) during the study period;Be willing and able to attend Victoria University (Melbourne, Australia) on one occasion for assessment.

Mid-portion Achilles tendinopathy will be diagnosed as per the clinical guidelines [7] and musculoskeletal ultrasound [25] using the following criteria:Report pain in the Achilles tendon during or after weight-bearing activities including walking, running or jumping/hopping;Pain in the Achilles tendon 2–6 cm proximal to the insertion (as described by the patient and palpated by the investigator);Gray-scale musculoskeletal ultrasound of the Achilles tendon(s) showing diffuse or local thickening (anterior–posterior) and/or irregular fibre orientation and/or hypoechoic areas within the mid-portion of the Achilles tendon. Certain features are commonly associated with mid-portion Achilles tendinopathy; however, may also exist in asymptomatic individuals [25]. Therefore, if participants exhibit the aforementioned sonographic features accompanied by fluid in the retrocalcaneal bursae (up to 4 mm), focal calcifications, paratenon thickening or calcaneal cortical anomalies (e.g. spurring); they will not be excluded [26].

Exclusion criteria:Currently pregnant;Previous Achilles tendon rupture or surgery in the symptomatic lower limb;Injury or pathology of the lower limb and/or back or any condition that, in the opinion of the investigators, may interfere with participation in the study (e.g. chronic ankle instability);Concurrent conditions (ankle or other region) that are more severe (pain numerical rating scale) than their worst mid-portion Achilles tendinopathy pain;Treatment with foot orthoses or heel lifts within the previous 3 months;Previous breast cancer/and or use of oestrogen inhibitors;Inflammatory arthritis (e.g. psoriatic arthritis);Neurological disorders (e.g. Charcot–Marie–Tooth disease);Taken fluoroquinolone antibiotics within the previous 2 years;Any injection (e.g. corticosteroid) into the Achilles tendon or surrounding area in the previous 3 months;Any medical condition that deems a participant unsuitable, based on the opinion of the investigators (e.g. type I or II diabetes).

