### Baseline assessment

The baseline assessments were derived from the ICON statement [18]. Participant characteristics (such as age, sex, ethnicity (including if identifies as a First Nations person), education and employment status), smoking status, major medical conditions, number of medications and presentation of tendinopathy (unilateral/bilateral and duration) will be recorded via a custom questionnaire. Height and weight will be measured using a stadiometer and digital scales and body mass index will be calculated as weight (kg)/height (m^2^). Static foot posture will be assessed using the Foot Posture Index (FPI) [27]. Ankle dorsiflexion range of motion will be assessed with a reliable lunge test technique [28]. Participants’ footwear will be assessed using selected items from the Footwear Assessment Tool [29] and their shoe size documented.

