### Interventions

#### Randomisation and blinding

Participants will be randomised to one of two groups: an intervention group (heel lifts) or a control group (sham heel lifts). Both groups will also receive the same guideline recommended education about activity modification. Using Sealed Envelope (https://www.sealedenvelope.com/), participants will be randomised on a 1:1 ratio with random permuted block sizes. Participants will be blinded via limited disclosure, as they will be told that the study will be comparing two types of ‘shoe inserts’. Primary and secondary outcomes will be self-reported; thus, this trial will be assessor blinded. The clinician (JB) administering the interventions will be unable to be blinded. The instructions on using the shoe inserts and education provided will be detailed in a brochure provided to the participants at baseline (Supplementary Material).

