### Statistical analysis

Statistical analysis will be performed using the most recent version of SPSS (IBM Corp., Armonk, NY, USA) available at the time of analysis. Data will be double entered to minimise errors. Demographic data and anthropometric characteristics (e.g. gender, age, foot posture using the FPI, etc.) will be reported by the treatment arm.

The intention-to-treat principle will be used for all participants [61]. Multiple imputation will be used to replace missing data for the primary and secondary outcome measures [62], with the exception being ‘Global Rating of Change Scale, where no data substitution will be applied. Standard tests to assess continuous data for normal distribution will be used and transformation performed if required. The primary outcome measure assessed will be pain intensity (at its worst) at 12 weeks. Continuously scored outcome measures (pain intensity (NRS-11), VISA-A, LEFS, EuroQol 5—VAS, IPAQ-SF and biomechanical outcomes) will be analysed using an ANCOVA with adjustment for baseline scores [63].

Dichotomous data (Global Rating of Change Scale, adverse events and use of co-interventions) will be compared using relative risk, absolute risk increase and number needed to treat or harm. Intervention adherence and CEQ data will be compared between groups using independent *t*-tests. To complement point estimates, standard deviations, 95% confidence intervals and *p*-values will be calculated where appropriate.

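### Symptom duration is recorded at baseline but left out of the stated ANCOVA; adding it as a pre-specified covariate is a nearly free, minor gain in precision

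*Protocol article*

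**What the plan says.** Four statements in the protocol article bear on this point.

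- **Eligibility criteria:** the only condition on chronicity is "Symptoms of mid-portion Achilles tendinopathy in one or both lower limb(s) for > 6 weeks". No upper limit is given.
- **Baseline assessment:** "presentation of tendinopathy (unilateral/bilateral and duration) will be recorded via a custom questionnaire". The value will therefore be in the dataset for every participant.
- **Randomisation and blinding:** "participants will be randomised on a 1:1 ratio with random permuted block sizes". No stratification factor is named.
- **Statistical analysis:** the continuous outcomes "will be analysed using an ANCOVA with adjustment for baseline scores". No further covariate is listed.

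On the course of the condition, Background and rationale cites recovery times of 21 to 479 days. It also states that "up to 60% of people with AT have continued pain and disability after 5 years despite exercise interventions". Both that section and the Discussion name natural history as a rival explanation for the earlier heel-lift result. The sham arm is the trial's answer to it.

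**The concern.** The entry rule allows a participant with seven weeks of symptoms and one with several years of symptoms to be randomised side by side with the same baseline pain score. If their expected 12-week courses differ, the baseline score cannot tell them apart and the difference goes into the residual.

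Two things follow in a trial of about 100 people:

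- The confidence interval for the primary comparison is wider than it need be.
- If one arm happens to receive more recent-onset cases, the stated model has no means of correcting for it. Adding duration after such an imbalance has been seen would be open to criticism as post hoc.

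Both depend on duration being prognostic for week-12 pain given baseline pain. That is plausible, but the documents do not establish it.

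**Working it through.** **Inputs.** From Sample size: difference 1.5 points, SD 2.3, f = 0.33, 90% power, alpha 0.05, 99 completers, 108 randomised, 10% drop-out. Assumed, because no figure is given: r, the partial correlation of (log) symptom duration with week-12 pain given baseline pain, from 0 to 0.4.

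**1. The plan's own figure.** For a two-arm ANCOVA with one covariate, power comes from the noncentral F distribution with λ = f²N and df = 1 and N − 3. With f = 0.33 and N = 99, λ = 0.1089 × 99 = 10.78 and power is 90.2%. The stated 99 reproduces. It takes no credit for variance explained by any covariate, since the full SD of 2.3 is used.

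**2. Baseline-only model at the expected number of completers.** 108 × 0.90 = 97.2, so 97. Unrounded f = 1.5/(2 × 2.3) = 0.326, λ = 0.326² × 97 ≈ 10.31, df = 1 and 94, power 88.9%. The small gap to 90% comes from rounding f and from the drop-out allowance (99/0.90 = 110, not 108). It is not caused by leaving duration out.

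**3. Adding duration.** Residual variance is multiplied by (1 − r²), f becomes 0.326/√(1 − r²), and df become 1 and 93. The SE of the difference is 2 × 2.3 × √(1 − r²)/√97.

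| r | fall in residual variance | SE | power, 97 completers | equivalent extra completers, 99/(1 − r²) − 99 |
|---|---|---|---|---|
| not in model | – | 0.467 | 88.9% | – |
| 0 | 0% | 0.467 | 88.8% | 0 |
| 0.1 | 1% | 0.465 | 89.1% | 1 |
| 0.2 | 4% | 0.458 | 90.0% | 4 |
| 0.3 | 9% | 0.446 | 91.5% | 10 |
| 0.4 | 16% | 0.428 | 93.4% | 19 |

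The first two rows show the price if duration is uninformative: 88.85% against 88.84%.

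**4. If 2.3 is a raw SD.** The table treats 2.3 as the SD left after baseline adjustment, which the protocol does not say. If it is a raw SD, baseline pain already shrinks it.

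| assumed baseline to week-12 correlation | power without duration | with r = 0.2 | r = 0.3 | r = 0.4 |
|---|---|---|---|---|
| 0.3 | 91.5% | 92.5% | 93.7% | 95.3% |
| 0.5 | 95.6% | 96.3% | 97.0% | 98.0% |

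**5. Chance imbalance.** With 97 analysed, the 95% range of the between-arm difference in duration is ±1.96 × 2/√97 = ±0.40 SD. At that edge, the baseline-only estimate shifts by 0.398 × r × 2.3, which is 0.09, 0.18, 0.27 or 0.37 points for r = 0.1, 0.2, 0.3 or 0.4. The target difference is 1.5 points.

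**6. Validity of the stated model.** In simulations of 10,000 null trials at N = 99, the model without duration rejected 4.9% of the time when duration explained 10% of the variance, and 5.0% when it explained 20%. Omitting it does not inflate type I error.

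**The case against.** The case against is strong, and much of it stands.

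- **No bias.** A reader might infer that natural recovery in recent-onset cases could systematically pass for, or hide, a heel-lift effect. The documents do not support that. Recovery common to both arms cancels in the comparison with a concurrent randomised sham arm given the same education. What remains is variation between people, and the ordinary standard error already allows for chance imbalance in it.
- **The recovery range proves little.** A reader might take the 21 to 479 days as the protocol saying that the condition resolves in that window, and work out from it how many recent-onset cases would recover during follow-up. The same section reports that up to 60% still have pain and disability at 5 years. It does not say whether the days run from onset or from the start of care. No share of recoveries can be derived from it.
- **The prognostic link is assumed.** Nothing in the protocol shows that prior duration predicts week-12 pain, and r could be zero.
- **Planned power does not need duration.** The 99 completers rest on the full SD of 2.3. If that SD fits this population, variation in recovery is already in it.
- **Scope.** ANCOVA on the baseline score is a standard primary analysis, and an analysis plan that is not shown may name further covariates.

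The last item does not dispose of the point. The article does more than leave the adjustment set open: it states one, and that set holds the baseline score alone. Adding a named, already collected variable is a specific change to a stated model, and its cost if it proves useless is negligible.

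**Conclusion.** The point holds as an optional efficiency gain, not as an error or a contradiction. The stated ANCOVA is valid and unbiased. Over assumed partial correlations of 0 to 0.4, including duration changes power at 97 completers from 88.9% to between 88.8% and 93.4%, and lowers the standard error by at most about 8% (0.467 to 0.428). These figures treat 2.3 as the residual SD; if it is a raw SD, the gains in power are smaller. Adjustment would also remove a chance shift of up to roughly 0.1 to 0.4 points at the edge of the 95% range for r of 0.1 to 0.4, and pre-specifying it avoids a later dispute over post hoc adjustment. Free improvement, minor severity.

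**What to change.** Before data lock, state in the analysis plan that the ANCOVA for worst pain at week 12 includes log-transformed symptom duration alongside the baseline score. Apply the same model to the other continuous clinical outcomes (VISA-A, LEFS, EQ-5D-5L VAS and IPAQ-SF). Keep the model with the baseline score alone as a sensitivity analysis. Since missing outcomes are to be multiply imputed, put duration in the imputation model as well, so that the two models agree. For participants with bilateral symptoms, say that the duration used is that of the side for which outcomes are reported.

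Eligibility and randomisation need no change. The cost is a line or two of analysis wording and one degree of freedom, with no new data collection. If duration proves not to be prognostic, nothing is gained and almost nothing is lost.

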### Baseline assessment

The baseline assessments were derived from the ICON statement [18]. Participant characteristics (such as age, sex, ethnicity (including if identifies as a First Nations person), education and employment status), smoking status, major medical conditions, number of medications and presentation of tendinopathy (unilateral/bilateral and duration) will be recorded via a custom questionnaire. Height and weight will be measured using a stadiometer and digital scales and body mass index will be calculated as weight (kg)/height (m^2^). Static foot posture will be assessed using the Foot Posture Index (FPI) [27]. Ankle dorsiflexion range of motion will be assessed with a reliable lunge test technique [28]. Participants’ footwear will be assessed using selected items from the Footwear Assessment Tool [29] and their shoe size documented.

### Interventions

#### Randomisation and blinding

Participants will be randomised to one of two groups: an intervention group (heel lifts) or a control group (sham heel lifts). Both groups will also receive the same guideline recommended education about activity modification. Using Sealed Envelope (https://www.sealedenvelope.com/), participants will be randomised on a 1:1 ratio with random permuted block sizes. Participants will be blinded via limited disclosure, as they will be told that the study will be comparing two types of ‘shoe inserts’. Primary and secondary outcomes will be self-reported; thus, this trial will be assessor blinded. The clinician (JB) administering the interventions will be unable to be blinded. The instructions on using the shoe inserts and education provided will be detailed in a brochure provided to the participants at baseline (Supplementary Material).

